### Interim analyses {21b}

In phase I, an interim analysis is planned when the first and second cohorts have been treated for 56 days with MFA. The interim analysis and interim report will describe subject recruitment, treatment compliance, and safety, tolerability, and the occurrence of any DLT for the subjects. Efficacy parameters will not be analyzed. After data cleaning and analysis, the interim report will be submitted to the data and safety monitoring board (DSMB) to obtain its advice regarding the MFA dose recommended for phase II. Phase II does not include an interim analysis.

### Methods for additional analyses (e.g., subgroup analyses) {20b}

Additional sensitivity analysis will be performed for survival endpoints in phase II (PFS and OS) including also the patients of the phase I part who received the same dose of MFA.

### Methods in analysis to handle protocol non-adherence and any statistical methods to handle missing data {20c}

In phase I, patients who are not evaluable for DLT will be replaced. A patient is evaluable for DLT if the DMSB has determined that a DLT has occurred in this patient during the first 56 days after treatment start (independent of the duration of MFA intake) or if until DLT visit (day 56 ± 3 days after start of MFA treatment) the patient has taken at least 100 doses of MFA (i.e., 89.3% of the maximally positive cumulative dose in 56 days) as documented by the patient’s diary and the documented return of 1 empty container of MFA (containing 100 capsules) (for dose step 2 × 100 mg daily or 2 × 50 mg daily) or of 2 empty containers of MFA (for dose step 2 × 200 mg daily).

In phase II, subjects dropping out of the trial prior to randomization will be listed as screening failures including the reason for dropout. Subjects prematurely discontinuing the trial will be censored regarding the analysis of PFS or OS at the time of discontinuation. Subjects dropping out after randomization will be analyzed using all available data and will not be replaced. The technique for the analysis of missing values will be defined in the statistical analysis plan. A check of a possible treatment effect on the frequency of missing values will be performed.

### Plans to give access to the full protocol, participant-level data, and statistical code {31c}

The study protocol and the informed consent forms will be made available on demand or through the website of the Division of Clinical Neurooncology, University of Bonn. Apart from that, the statistical analysis plan and the clinical study report will be made available. Participant-level data will be shared beginning 6 months and ending 3 years following article publication. Data are made available to researchers after a methodologically sound scientific proposal has been submitted to the coordinating investigator; a steering committee consisting of the coordinating investigator, the representative of the coordinating investigator, and a SZB member has approved the proposal; and a data access agreement has been signed. After 36 months, the data will be available in our university’s data warehouse but without investigator support other than deposited metadata.

## Oversight and monitoring

### Composition of the coordinating center and trial steering committee {5d}

To ensure accurate, complete, consistent, and reliable data, the investigator’s site(s) and trial procedures will be monitored by a representative of the sponsor.

The sponsor’s representative or his delegate will visit the site and oversee the following things: evaluation of the progress and recruitment of the trial; review of source documents and case report forms (CRFs) for protocol compliance, accuracy, and validation; assessment of facilities and equipment; check for protocol compliance; check for correct and timely AE/SAE and DLT reporting; verifying of proper handling and dispensing of the investigational medicinal product (IMP); and other factors.

Source data verification will be performed in order to verify the accuracy and completeness of the entries on the CRF by comparing them with the source data, and to ensure and increase the quality of the data. All data which are subject to source data verification (SDV) must have been entered in the medical record or, in the case of source documents, enclosed with the medical record. The investigators will provide access to the medical records for the performance of SDV.

Frequency and scope of the monitoring visits will be defined in the Monitoring Plan for this trial which also includes the extent of source data verification that is required.

### Composition of the data monitoring committee, its role, and reporting structure {21a}

There will be an independent data and safety monitoring board consisting of a neurooncologist, a neurosurgeon, a medical oncologist, and a statistician. It will review safety data and recruitment data. It will also provide a recommendation for the further proceeding of the trial to the sponsor. Meetings of this board are planned for evaluating DLT data of phase I after each dose step when all patients in this dose step are evaluable for DLT, about 6 months after recruitment of the first patient of phase II, and after all patients have concluded MFA therapy. Of course, the sponsor or the DSMB itself can schedule additional meetings at any timepoint.

### Adverse event reporting and harms {22}

Any AE and SAE (per definition in the trial protocol) has to be documented in the CRF on the respective adverse event report form. AE/SAE documentation will be performed for each participant between the baseline visit and the visit at least 3 days after termination of MFA administration. AEs will be reported and evaluated according to the Common Terminology Criteria for Adverse Events (CTCAE5). According to the GCP-V, only AEs and unexpected clinical diagnostic findings that are identified in the protocol as critical for clinical trial evaluation must be documented and transmitted to the sponsor. To ensure comparability of the safety data of the two study arms, any adverse medical incident in patients of the control arm will also be recorded although no study drug will be administered. Whenever possible, diagnoses should be given when signs and symptoms are due to a common etiology. All measures required for adverse event management must be recorded in the source document and reported according to sponsor’s instructions. The investigator evaluates all AEs regarding severity, causality, and seriousness. Every SAE has to be reported immediately via fax to the Study Coordinating Center at the SZB. To take into account safety data available to the sponsor but not to the investigator at the time the SAE was detected, in addition to the initial assessment of a SAE by the investigator, a second assessment of the event by the sponsor in terms of causality and probability of occurrence (“expectedness”) and a continuous benefit-risk assessment are performed.

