### Trial design {8}

The study consists of a single-arm phase I part and a randomized, parallel-group, and unblinded phase II part.

In phase I, patients with the first relapse of MGMT-methylated glioblastoma are screened for the trial. After inclusion, patients are pretreated with MFA in addition to standard TMZ and tumor resection will be performed 7–10 days after initiation of therapy. MFA tissue level measurements and translational analyses are performed on the tumor material obtained from resection. Each patient is particularly screened for dose-limiting toxicities (DLTs) during the first 8 weeks of his/her MFA treatment. Patients are recruited in two cohorts of three to six patients. Dose adaptation in between cohorts depends on the occurrence of DLTs as described below.

All patients of phase I are followed for toxicity and efficacy until the end of phase II.

In phase II, patients with the first relapse of MGMT-methylated glioblastoma are screened for the trial. After inclusion, patients are randomized (1:1) into two parallel groups, the experimental or the standard treatment arm. The experimental treatment is defined as treatment with MFA (dose determined in phase I) in addition to standard TMZ. The standard treatment arm is defined as monotherapy with TMZ (150–200 mg/m^2^ body surface). If tumor resection for the relapsed tumor is clinically indicated, the local treating neurosurgeon can decide whether the resection can be safely postponed until day 7–10 after initiation of therapy (optional, not a prerequisite for study participation in phase II) and tumor material for determination of MFA levels can be obtained.

MFA is taken at the dose determined in phase I. Daily MFA treatment is continued for 8 4-week courses (i.e., 224 days), until tumor progression, until the occurrence of a DLT attributable to MFA, or until definitive discontinuation of standard TMZ, whatever comes first. In case MFA therapy is terminated, standard TMZ therapy can be continued at the discretion of the treating physician.

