**Table 1 Tab1:**
[figure not shown]
Visits and assessments in the MecMeth/NOA-24 trial

*DLT visit will only be performed in phase I. In phase I, visit 2.3 is only performed additionally; if the start of cycle 3 is prolonged for more than 3 days after the DLT visit, all patients in phase II have visit 2.3

**EoT: end of treatment is reached 3 days after last MFA intake (phase I and experimental arm of phase II) or on day 31 of the last TMZ cycle (standard arm of phase II)

***End of study and of follow-up in the entire trial will be reached when *both* of the following requirements are fulfilled: (1) at least 6 months after randomization of the last patient in phase II *and* (2) at least 3 days after definite termination of MFA intake in the last patient receiving MFA therapy (i.e., all patients have concluded study-related MFA intake for more than 3 days)

^1^Every 8 weeks: progression assessment, Karnofsky score and QoL, blood samples

^2^Na, K, creatinine, ASAT, ALAT, bilirubin

^3^Gadolinium-enhanced MRI obtained prior to inclusion/randomization can be used as baseline MRI if the interval between this MRI and the start of study therapy is shorter than 21 days. In patients who have undergone re-resection prior to randomization (only possible in phase II), the MRI used as baseline MRI has to be a postoperative MRI

^4^Relapse tumor resection 7–10 days after initiation of study therapy, tissue asservation should take place 2–4 h after the last intake of MFA/TMZ: (1) fresh frozen, (2) 4% PFA, and (3) FFPE tumor material for MFA/MFA metabolite level determination and for analysis of MFA-dependent tissue effects. The exact timepoint of the last MFA intake prior to resection and the exact timepoint of asservation of the tumor material have to be documented

^5^Timepoints (to be documented): (a) 2 h after first intake, (b) on the days between MFA start and resection daily blood sampling 2 h after morning application of MFA (optional), and (c) on the day of resection 5 blood samples at an interval of 2 h (0 h (prior to last preOP MFA dose) 2 h, 4 h, 6 h, 8 h later)

^6^Only at the first follow-up visit after discontinuation of MFA

^7^Only during ongoing MFA treatment + 3 days

^8^Only if clinically indicated

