Briefly, patients start therapy within 7 days after inclusion/baseline visit. If according to the local treating neurosurgeon and the local neurooncological tumor board, re-resection of the tumor is clinically indicated and can be safely deferred until day 7–10 after initiation of MFA/TMZ therapy, tumor resection is performed 7–10 days after initiation of therapy. This is mandatory in phase I and optional in phase II. Resected tumor tissue is used for translational analyses of intratumoral MFA/MFA metabolite levels and detection of cellular and molecular effects of MFA. Also, blood analyses are performed for the determination of MFA blood levels 2 h after the first intake of MFA on day 1 and at 5 timepoints on the day of resection. During therapy, further visits are scheduled every 4 weeks prior to the start of a new TMZ cycle. These visits include clinical and standard laboratory examinations, documentation of co-medication documentation of (S)AE, KPS, and, every 8 weeks, contrast-enhanced MRI and QoL evaluation. In phase I, DLT evaluation is added at the visits prior to cycle 2 (day 28 ± 3) and cycle 3 (day 56 ± 3). MFA/TMZ treatment ends after 8 4-week cycles, at progression, or if MFA or at the timepoint when MFA or TMZ treatment has to be prematurely discontinued for whatever reason, e.g., intolerable toxicity, whatever comes first. After the end of the study therapy, patients are followed with clinical examination, contrast-enhanced MRI, and documentation of KPS, QoL, and further tumor therapy every 8 weeks. End of study and of follow-up in the entire trial will be reached when both of the following requirements are fulfilled: (1) at least 6 months after randomization of the last patient in phase II and (2) at least 3 days after definite termination of MFA intake in the last patient receiving MFA therapy (i.e., all patients have concluded study-related MFA intake for more than 3 days).

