### Plans to promote participant retention and complete follow-up {18b}

To promote participant retention and complete follow-up, patients will be closely monitored. Besides, they will always have the chance to contact a responsible person at the site. Contact data (telephone numbers, email) will be given to the patient at the beginning of the trial. If participants decide to discontinue MFA treatment, they will be asked to stay in the follow-up for their own safety and to obtain follow-up data (AE, PFS, OS). If they are not willing to do so, the investigator is urged to ask the subject to return for an early termination visit and to document subject outcome (AE, PFS, OS), if possible. Any clinically significant abnormalities persisting at withdrawal will be followed by the investigator until resolution or until reaching a clinically stable endpoint. If a subject does not return for a scheduled visit, every effort will be made to contact the subject.

Subjects may also be withdrawn at any time at the discretion of the investigator for safety, behavioral, or administrative reasons. All patients who are discontinued from study therapy for any reason have to be followed according to the study protocol with clinical and MRI investigations until the end of the follow-up time of the whole trial (including the collection of all outcome data as described above).

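### The AE/SAE recording window is tied to MFA, so it is undefined for controls, can end earlier than TMZ in the experimental arm, and conflicts with the follow-up sections

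*Protocol article*

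**What the plan says.** Adverse event reporting and harms {22} gives a single rule for everyone: "AE/SAE documentation will be performed for each participant between the baseline visit and the visit at least 3 days after termination of MFA administration". The same section says that events in controls are recorded too, so that the arms can be compared, but gives no end date for them.

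The footnotes to Table 1 define end of treatment by arm. For MFA patients, "end of treatment is reached 3 days after last MFA intake (phase I and experimental arm of phase II"; for controls, "or on day 31 of the last TMZ cycle (standard arm of phase II".

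Four other sections bear on what happens once MFA stops:
- Trial design {8}: "In case MFA therapy is terminated, standard TMZ therapy can be continued at the discretion of the treating physician". It also says that phase I patients are followed for toxicity until phase II ends.
- Participant timeline {13}: study therapy ends, among other reasons, "at the timepoint when MFA or TMZ treatment has to be prematurely discontinued for whatever reason". Its list of assessments after study therapy does not include adverse events.
- Plans to promote participant retention {18b}: of patients who decide to stop MFA, "they will be asked to stay in the follow-up for their own safety and to obtain follow-up data (AE, PFS, OS". It further requires everyone taken off study therapy to be followed to the end of the trial, with all outcome data collected.
- Statistical methods {20a}: adverse events are summarized descriptively, by patients and by MFA/TMZ courses given.

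**The concern.** A safety comparison between randomized arms needs the same observation rule in both. Here the rule depends on a drug that only one arm takes. An experimental patient who stops MFA but stays on TMZ can leave event recording soon afterwards, while a control on the same TMZ schedule has no such cut-off. The patients affected are partly selected by toxicity, because {11b} lists MFA-related toxicity among the reasons for stopping MFA.

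Safety and tolerability are phase II objectives {7}, and adverse event monitoring is a phase II secondary outcome {12}. Events that were never recorded cannot be recovered at analysis, so this cannot be left to the statistical analysis plan. Sites that work from {22} and sites that work from {18b} would also collect different data.

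**Working it through.** **Inputs.** MFA is planned for 8 courses of 4 weeks {8}, and TMZ for eight 28-day cycles {11a}. Recording ends at least 3 days after the last MFA dose {22}; the minimum of 3 days is used here. The control end point is taken from the end-of-treatment footnote to Table 1, because no explicit end of event recording is given for controls.

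**The plan's own figure.** 8 × 28 = 224 days, as stated in {8}.

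**Where the windows agree.** If both drugs end at the close of cycle k:
- experimental: 28k + 3
- control: 28(k − 1) + 31 = 28k + 3

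These are identical. For k = 8 both give day 227.

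**Where they differ.**
- MFA stops on day d of the last TMZ cycle: the gap is 31 − (d + 3) = 28 − d days. For d = 14 that is 14 days.
- MFA stops at the end of cycle k and TMZ runs to cycle 8: the gap is 227 − (28k + 3) days. That is 168 days for k = 2, 112 for k = 4 and 56 for k = 6.

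**Loss at arm level.** The documents give no rate of early MFA stopping. Assume that a share q stops after cycle k and continues TMZ to cycle 8, and that all others complete eight cycles. Then loss = q × (227 − (28k + 3)) / 227.

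| q | k = 2 | k = 4 | k = 6 |
|---|---|---|---|
| 5% | 3.7% | 2.5% | 1.2% |
| 10% | 7.4% | 4.9% | 2.5% |
| 20% | 14.8% | 9.9% | 4.9% |
| 30% | 22.2% | 14.8% | 7.4% |

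**Direction, for q = 20% and k = 2 (assumed).** Observed courses per experimental patient are 0.8 × 8 + 0.2 × 2 = 6.8 of 8. The other 1.2 are TMZ courses after MFA.
- Equal true event rates: the crude count ratio is 6.8/8 = 0.85 instead of 1.00, which favors MFA. Per observed course it is 6.8/6.8 = 1.00. If the TMZ courses after MFA are counted in the denominator while their events are not collected, it is again 6.8/8 = 0.85.
- Rate 1.5 times control on MFA and equal to control afterwards: the complete ratio is (6.8 × 1.5 + 1.2 × 1.0)/8 = 1.425. The truncated ratio per observed course is 1.50, which goes against MFA.
- Rate 1.5 times control on MFA and 2 times control afterwards: the complete ratio is (6.8 × 1.5 + 1.2 × 2.0)/8 = 1.575. The truncated ratio per observed course is 1.50, which favors MFA.

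In the last two cases the truncated crude ratio is 10.2/8 = 1.275, below the complete value both times.

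**The case against.** The strongest reply is that {18b} already requires what seems to be missing. It asks for adverse event data after MFA is discontinued, and it makes follow-up with all outcome data mandatory for anyone off study therapy; {12} lists adverse event monitoring among the outcomes. This stands, and it rules out treating the loss of follow-up as settled. What remains is a conflict: {22} is the section that governs event recording, and it says something else.

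Other parts of the reply also stand. The 3 days are a minimum tied to a visit. The arms are aligned whenever both drugs end at a cycle's close. Day 31 is an end-of-treatment definition, so the control recording end is inferred. Table 1 has a footnote reading "Only during ongoing MFA treatment + 3 days", but the row that it marks is not visible, so nothing is built on it. {8} and {13} on TMZ after MFA may be compatible if {13} means only that study therapy ends; the text does not make this clear.

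The loss table assumes that all other patients complete eight cycles. The sample size section assumes a control PFS-6 of 40%. If PFS is exponential and 6 months are about 183 days, 0.40^(224/183) ≈ 0.33 of controls would be progression-free at day 224. The percentages are therefore illustrations and not forecasts.

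A reader might infer that the randomized safety comparison is biased in favor of MFA. The documents do not support that as a general statement. It follows for crude counts if {22} is applied literally. Per course, the direction depends on the event rate after MFA stops and on which courses are counted, and {20a} does not settle the second point.

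**Conclusion.** The defect holds in a limited form. The window in {22} has no meaning for controls. It uses a different anchor from the control end point in Table 1, and it contradicts {18b} and, for phase I patients, the toxicity follow-up in {8}. Followed as written, it can under-record events in experimental patients who stop MFA mid-cycle or continue TMZ without it. The gap reaches 168 days for a stop after cycle 2 with TMZ to cycle 8, and is zero for completers.

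Across the assumed range of 5% to 30% stopping after cycle 2, the experimental arm loses 3.7% to 22.2% of its observation time; for stops after cycle 6 the range is 1.2% to 7.4%. These figures rest on the minimum of 3 days, the inferred control end point and completion by all others.

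The point concerns secondary, descriptive safety outcomes. The PFS analysis, power and alpha are unaffected, and the phase I dose decision has its own 56-day DLT rule {20c}.

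**What to change.** - In {22} and Table 1, keep the start at the baseline visit and define one AE/SAE window for both arms. It should end the same interval after the last dose of any trial treatment (TMZ or MFA), and at least through day 31 of the final TMZ cycle, whether or not MFA has stopped. For patients given eight TMZ cycles with MFA stopped no later than TMZ, coverage then runs to at least day 227 in both arms, and the gap between arms is zero by construction.
- In {20a}, state that adverse events are reported per patient and per course or time observed within that window, so that the denominator matches what was recorded.
- Reconcile {8}, {13}, {18b} and {22} on whether TMZ continues and how long adverse events are followed after MFA is discontinued, including the longer toxicity follow-up for phase I patients.

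The cost is protocol and CRF wording and some extra adverse event entry at visits that are already scheduled.

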### Frequency and plans for auditing trial conduct {23}

This trial may be selected for audit by representatives of the sponsor or, independent from the sponsor, for inspection by site responsible representatives of the local regulatory authority. There is no predefined schedule for audits and inspections. After every audit, the auditee(s) will receive an audit confirmation by the auditor. This document has to be filed together with the trial documentation and has to be made available also to the authorities in case of an inspection. At the end of the trial, a copy of the audit certificate(s) will be included in the final report.

### Plans for communicating important protocol amendments to relevant parties (e.g., trial participants, ethical committees) {25}

The sponsor can implement changes to the protocol after the clinical trial has started. These may be administrative (logistical/administrative amendments) or substantial. Substantial amendments (e.g., those who can affect the safety or physical or mental integrity of participants or the scientific value of the trial) require a new authorization of the national competent authority and a new favorable opinion by the Ethics Committee (EC). The participants will be informed about substantial amendments and, if applicable, an updated Informed Consent Form has to be signed by all subjects enrolled in the trial who are affected by the amendment.

Amendments which only have to be approved by the EC (e.g., changes in an advertisement for subjects to participate in the trial or changes in facilities for the trial) also will be notified to the national competent authorities (NCA) with the comment “For information only.” Similarly, the EC will be informed of any substantial amendments for which only the NCA is responsible (e.g., quality data). If administrative protocol changes (e.g., change of monitoring, telephone numbers) are necessary, the EC and NCA will be notified only. All amendments will be communicated to the participating trial centers.

